### Ethics

The trial protocol has been approved by the primary institution’s Human Research Committee (protocol number: 2020P000322). The protocol has been registered on ClinicalTrials.gov (ID: NCT04330391). All participants will provide verbal and/or written consent prior to enrollment in the study.

### Randomization and allocation

Enrolled subjects will be randomized into two groups with an allocation ratio of 1:1 in blocks of four. The allocation table will be randomly generated via Microsoft Excel by an independent third-party clinical researcher, uploaded to the study REDCap randomization model, and will not be accessible to study staff within REDCap. Group assignment will be revealed via the REDCap model only at the time of randomization during enrollment following informed consent procedures and enrollment BMI verification.

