## Abstract

**Background:**

The months prior to elective surgery may present an opportunity for patients to initiate behavior changes that will simultaneously ready them for surgery and improve their overall health status. An upcoming elective total joint arthroplasty (TJA) may serve as motivation for patients with severe obesity (body mass index [BMI]> 40 kg/m^2^) to lose weight, as it may optimize clinical outcomes following TJA and help them become eligible for TJA since some surgeons use a BMI of 40 kg/m^2^ as a cut-off for offering surgery in an effort to optimize outcomes.

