## Background

Surgery is a major decision for many patients and often involves reflection on personal health behaviors when weighing the risks and benefits of procedures [1, 2]. Positive preoperative lifestyle factors including nonsmoking status, increased physical activity, and normal body mass index (BMI) are associated with improved postoperative outcomes [3–5]. However, time pressure, fiscal constraints, and limited provider experience encouraging lifestyle changes may hamper effective counseling during the preoperative period [6, 7]. Digital technologies have recently been proposed as a potential solution to the barriers of preoperative lifestyle counseling [2].

A previous remote dietitian (RD) intervention for overweight pregnant women in 2018 demonstrated high satisfaction with dietitians and a desire for an integrated mobile app before a motivating event like childbirth [8]. An upcoming elective surgery may be similarly motivating for patients to make lifestyle modifications, especially for patients with severe obesity who may become eligible for surgery if they reduce their BMI below the 40 kg/m^2^ maximum for total joint arthroplasty (TJA) used by some surgeons as a cutoff for offering surgery in an effort to optimize outcomes [9].

A recent retrospective review of patients with severe obesity (BMI > 40 kg/m^2^) who lost weight before total knee arthroplasty (TKA) found that losing at least 20 pounds before surgery was associated with fewer discharges to a facility and shorter lengths of stay, but losing just five or 10 pounds had no effect [10]. A 2018 study of physical activity after TKA found a combined dietitian and financial incentive intervention increased step counts and physical activity following TKA [11].

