## Methods/design

### Study design

This mixed-methods study is a prospective, two-arm, randomized controlled trial that will take place remotely and involve patients at two institutions. The trial includes a 12-week intervention period followed by a 3-month follow-up period for selected secondary outcomes. Various outcomes will be assessed at baseline, 6 weeks, 12 weeks, and 24 weeks (Fig. 1).

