Individuals randomized to the clinical standard of care group will receive care according to current clinical guidelines. This may include a physical therapist and/or nutritionist referral, of which several programs within the institutions are offered to patients interested in weight loss, including the Nutrition Wellness Service (NWS) and Program for Weight Management (PWM).

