#### Secondary outcome measurement

##### Weight and related measures

Weight-related secondary outcomes will include: percent weight (kg) change, BMI change, percentage of patients losing at least 20 pounds, percentage of patients eligible to undergo TJA by BMI < 40 kg/m^2^ at 3 months after study enrollment, number of weeks (up to 6 months) after enrollment until eligible for TJA by BMI < 40 kg/m^2^, number of dietitian calls until eligible for TJA by BMI < 40 kg/m^2^, and weight at 3-month post-operative visit when available. The percentage of patients undergoing TJA within 6 months of study enrollment will be calculated by review of each subject’s electronic medical record.

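### As described, neither the allocation nor the stated tests account for institution in this two-site, 60-patient trial: no systematic bias, but an avoidable minor weakness, mainly for surgery within 6 months

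*Protocol article*

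**What the plan says.** The protocol article (Study design) describes a two-arm randomized trial "that will take place remotely and involve patients at two institutions".

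Under Randomization and allocation it states: "Enrolled subjects will be randomized into two groups with an allocation ratio of 1:1 in blocks of four". It goes on: "The allocation table will be randomly generated via Microsoft Excel by an independent third-party clinical researcher". The same section covers the upload to REDCap, concealment from study staff and the moment at which assignment is revealed. It names no stratification factor.

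The section on Statistical analyses lists t tests for continuous outcomes and chi-square or Fisher tests for categorical ones, with no term for institution.

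On usual care, the Arms section says: "This may include a physical therapist and/or nutritionist referral, of which several programs within the institutions are offered to patients interested in weight loss". On surgeon policy, the abstract says that "some surgeons use a BMI of 40 kg/m^2^ as a cut-off for offering surgery". One dietitian treats all intervention participants (Quality control and safety monitoring).

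On surgery as an outcome, the list of secondary outcomes says: "The percentage of patients undergoing TJA within 6 months of study enrollment will be calculated by review of each subject’s electronic medical record". A higher percentage having TJA within 6 months is the third of the three stated hypotheses.

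**The concern.** Blocks of four drawn from one pooled list balance the arm totals. They do not balance the arms within each institution. If outcomes differ by institution and one arm happens to draw more of its patients from one of them, part of the observed arm difference belongs to the institution. An analysis without a site term cannot separate the two.

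The outcome most exposed is receipt of TJA within 6 months. It depends on the patient's weight, but also on whether the surgeon applies a BMI cut-off and on when an operating slot is available. Both can be local. Weight change is less exposed: a site could affect it through the referrals that make up usual care, while a single dietitian delivers the intervention to everyone. Eligibility by BMI below 40 uses one fixed threshold for all patients, so surgeon policy does not enter it.

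**Working it through.** **Inputs from the protocol article.** 60 patients, 30 per arm, 1:1 in blocks of four, two institutions; planning difference 3.38 + 2.01 = 5.39 kg; SD 6.62 kg; 80% power; significance level 0.05 (two-sided assumed).

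**Inputs assumed, because the article does not give them.** Site split 50/50 to 90/10; difference in mean weight change between sites 0, 2 or 4 kg; difference in 6-month TJA rate between sites 30 points; overall TJA rate 25% to 50%.

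**1. The plan's own figure.** n per arm = 2 × (1.960 + 0.842)² × 6.62² / 5.39² = 23.7, so 24. This reproduces the stated 24 per arm. The sample size is not in question here.

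**2. How large a chance site imbalance is.** If site is unrelated to position on the list, the difference in site share between arms has mean 0 and SD √(2p(1−p)/30), where p is one site's share. For p = 0.5 this is √(0.5/30) = 0.129; for p = 0.8 it is √(0.32/30) = 0.103. Simulation of 50,000 pooled lists of 60 gives the same SDs and these probabilities:

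| Site split | SD of imbalance | P(gap ≥ 10 points) | P(gap ≥ 20 points) |
|---|---|---|---|
| 50/50 | 0.129 | 52% | 16% |
| 70/30 | 0.118 | 48% | 12% |
| 80/20 | 0.103 | 42% | 8% |
| 90/10 | 0.078 | 28% | 2% |

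With one list of blocks of four per site, the SD falls to 0.022 (50/50) and 0.025 (80/20), and no simulated trial had a gap of 10 points or more.

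**3. Effect on TJA within 6 months.** Shift = imbalance × site difference = 0.20 × 30 points = 6 points. The standard error of a difference in proportions with 30 per arm is √(2q(1−q)/30): 11.2 points at q = 25%, 12.6 at 40% and 12.9 at 50%. So 6 points is 0.46 to 0.54 standard errors.

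**4. Effect on weight.** With a 20-point imbalance and a site difference of 2 to 4 kg, the shift is 0.20 × 2 = 0.4 kg to 0.20 × 4 = 0.8 kg, or 7% to 15% of 5.39 kg. The standard error is 6.62 × √(2/30) = 1.71 kg.

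**5. Type I error and power for weight** (40,000 simulated trials per setting, 30 per arm, all completing). With the pooled list and plain t test, type I error is 5.1% at a site difference of 2 or 4 kg, and the mean estimate is unbiased. Power is as follows:

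| Site difference | Split | Pooled list, t test | Stratified list, t test |
|---|---|---|---|
| 2 kg | 50/50 | 86.6% | 86.7% |
| 2 kg | 80/20 | 86.8% | 87.1% |
| 4 kg | 50/50 | 84.4% | 85.1% |
| 4 kg | 80/20 | 85.5% | 86.0% |

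Stratifying and also adjusting for site brings power back to about 87%. That is a gain of less than 1 point at 0 to 2 kg and of about 1 to 3 points at 4 kg. Stratifying without adjusting makes the t test slightly conservative (type I error 4.1% at 4 kg, 50/50), so the two changes belong together.

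**The case against.** The strongest reply has four parts.

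- **Silence.** The article never says that the list is unstratified or that both sites share one list. A single allocation table could hold a site column, and a fuller protocol or analysis plan might specify this. That stands as a limit on certainty, so the point is confined to the method as described. But the description is detailed: it gives ratio, block size, software, list maker, upload and concealment. A stratum would normally appear beside the block size.
- **No documented site difference.** The article says that "several programs within the institutions are offered to patients interested in weight loss", without saying that the programs differ between the two. The cut-off is described as "used by some surgeons as a cutoff for offering surgery in an effort to optimize outcomes", which is general background and not an account of these two institutions. This stands. A reader might infer that the institutions do differ in usual care or surgical policy; the document shows only that they could.
- **Chance imbalance is not bias.** This stands in full. A reader might infer that the comparisons are distorted. They are not: allocation is random and concealed, the imbalance averages zero, and ordinary standard errors already allow for it. For weight, the loss of power is negligible unless the sites differ by several kilograms.
- **Stratifying has a cost of its own.** Participants are unblinded, and fixed blocks of four run separately at each site are easier to predict than a pooled list. In a block of four, the last assignment follows from the first three, and the third follows from the first two whenever those match (2 of 6 arrangements). This stands, and the fix has to deal with it.

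**Conclusion.** The point holds in a limited form and is minor. As described, a two-institution trial of 60 patients takes account of site in neither allocation nor analysis. The result is exposure to chance imbalance, with no systematic bias and no inflation of type I error.

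The case rests mainly on TJA within 6 months. There an imbalance that occurs in roughly one trial in twelve (80/20) to one in six (50/50) would move the result by about half a standard error. That size depends on the assumed 30-point difference in site TJA rates and scales with it: a 15-point difference would give 3 points. For the primary weight comparison the shift is at most about half a standard error (0.8 / 1.71 = 0.47), and only under the assumed 4 kg site difference. The argument from surgeon policy does not extend to eligibility by BMI below 40.

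The change is still worth making. It is nearly free, and settling it in advance avoids a dispute after the fact if the sites turn out uneven.

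**What to change.** State whether the allocation table is stratified by institution. If it is not:

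- **Before enrollment starts:** generate the table separately for each institution, with block sizes that vary at random and are not disclosed to enrolling staff, and load it into REDCap with institution as the stratification field.
- **In the analysis:** include institution as a factor in the comparison of weight change (a linear model with arm and institution in place of the t test), and as a stratum for TJA within 6 months, for example by Mantel-Haenszel.
- **If enrollment has already started:** keep the existing list and make only the analysis change, before group assignments are unblinded for analysis.

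The cost is two lists instead of one, one degree of freedom in the weight model, and slightly unequal arm totals from an incomplete last block at each site. The required sample size does not change. If the sites turn out not to differ, adjusting for institution on the existing pooled list costs less than 1 point of power for weight (87.3% to 86.7% in simulation).

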### Patient population and recruitment procedure

Patients of fellowship trained arthroplasty surgeons at two institutions will be identified as potentially eligible for the study based on 40 kg/m^2^ < BMI < 47 kg/m^2^ recorded in the patient’s medical record within the last 6 months and recommended primary, unilateral total knee or hip arthroplasty. For patients identified as potentially eligible while in clinic, an orthopaedic surgeon will introduce the patient to the study, and a member of the research team (research assistant or trainee) will conduct an eligibility screening and obtain verbal consent either in-person or by phone. For patients identified as potentially eligible outside of clinic, a member of the research team will call the patient to introduce the study, and conduct eligibility screening and consent on the phone.

Eligible, interested, and consented patients will be provisionally enrolled, and all subjects will be shipped a standard bathroom scale to their home (Fig. 1). This initial enrollment is provisional, as subjects will be required to verify enrollment BMI by (a) submitting a photo to the study team of their study scale during a weigh-in that displays their body weight, or by (b) recording a baseline weight at an onsite healthcare facility within 2 weeks of provisional enrollment. Once enrollment BMI is verified to be 40 to 47 kg/m^2^, subjects will be fully enrolled and randomized to the intervention arm or clinical standard of care arm via REDCap. Subjects will be given a $40 check for enrolling, which includes (1) taking a baseline survey, (2) recording the baseline weight at an onsite healthcare facility or with a home study scale, and (3) getting baseline labs within 2 weeks of the baseline weight. Baseline weights will be recorded without shoes or outer clothing (e.g., coats). All subjects will be given a $20 check if they can verify a mid-study weight during week 6 of the study by recording a weight at any onsite healthcare facility or by submitting home study scale photos. All subjects will receive a $40 check for completing an end-of-study survey, weight, and labs at 10–14 weeks after enrollment.

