### Blinding

Any staff involved in weighing participants or obtaining labs, as well as the principal investigator will be blinded from the group assignment until statistical analyses are finished. The subjects will not be blinded due to the nature of the study. While adverse events (AEs) are unexpected given the minimal risk of the study, if an AE potentially related to the intervention occurs, the principal investigator will decide whether the group assignment for a particular subject should be revealed.

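### A single, published block size of four could let a recruiter who follows past assignments be certain of up to one third of them; varied, undisclosed sizes would largely remove this

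*Protocol article*

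**What the plan says.** Under Randomization and allocation the protocol article fixes one block size: "Enrolled subjects will be randomized into two groups with an allocation ratio of 1:1 in blocks of four". It names no varying sizes and no stratification factor. The same section sets real safeguards. An independent third party generates the table, which is "uploaded to the study REDCap randomization model, and will not be accessible to study staff within REDCap". In addition, "Group assignment will be revealed via the REDCap model only at the time of randomization during enrollment", after consent and verification of BMI.

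On who knows the assignments, the Blinding section says "The subjects will not be blinded due to the nature of the study". It limits blinding of staff to certain roles: "Any staff involved in weighing participants or obtaining labs, as well as the principal investigator will be blinded from the group assignment". Recruitment is done by someone else. Under Patient population and recruitment procedure, "a member of the research team (research assistant or trainee) will conduct an eligibility screening and obtain verbal consent". That role is not in the blinded list.

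Randomization does not follow consent at once. Patients are first enrolled provisionally and must verify their weight by a scale photo or an onsite weighing. Then: "Once enrollment BMI is verified to be 40 to 47 kg/m^2^, subjects will be fully enrolled and randomized". The trial will "involve patients at two institutions" (Study design). The article does not say whether they share one allocation list.

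**The concern.** Hiding the table prevents staff from reading the next assignment. It does not prevent them from working it out. With a known block size of four and two places per arm, anyone who has seen two assignments to the same arm in a block knows the rest of that block. The fourth place is always known.

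Two features of this trial make that usable in principle. Assignments become visible as they are made: participants know their arm, and those in the intervention arm are linked to the dietitian at enrolment (Arms). There is also an interval between consent and randomization, in which the effort put into a patient, or the moment a weight is processed, could be influenced by an expected assignment.

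The primary outcome is weight change under a behavioural programme, for which motivation is a plausible driver. If more motivated patients tended to enter when an intervention place was expected, the arms would differ before treatment began. The Statistical analyses section plans t tests for the continuous weight outcomes and mentions no covariate adjustment.

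**Working it through.** **Inputs.** Block size 4 and ratio 1:1 (Randomization and allocation); 30 per arm, 60 in all (Sample size calculation); two institutions (Study design). The article gives no figure for predictability, so there is none to reproduce.

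**Step 1: certain assignments in a block of four.** With I for intervention and C for control, there are six equally likely sequences, so 6 × 4 = 24 positions.
- IICC and CCII: positions 3 and 4 are forced, 2 × 2 = 4 positions.
- ICIC, ICCI, CIIC and CICI: only position 4 is forced, 4 × 1 = 4 positions.

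Total: 8/24 = 33.3%. Over 60/4 = 15 blocks this is 15 × 4/3 = 20 expected assignments. Every completed block contains at least one.

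**Step 2: best-guess accuracy.** Always guess the arm with fewer patients so far in the block.
- Position 1: 1/2.
- Position 2: 2/3.
- Position 3: certain in 1/3 of blocks and even odds in 2/3, so 1/3 + (2/3)(1/2) = 2/3.
- Position 4: 1.

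Mean: (1/2 + 2/3 + 2/3 + 1)/4 = 17/24 = 70.8%, against 50% under simple randomization.

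**Step 3: a recruiter who sees only one site.** Suppose both institutions draw on one list, and a recruiter sees own-site assignments only but knows the position in the block. Let q be that site's share of patients. A place is forced for this recruiter only if both earlier patients in the filled arm came from that site (probability q²). The share certain is (q²/3 + q²)/4 = q²/3.
- q = 0.75: 0.5625/3 = 18.8%.
- q = 0.50: 0.25/3 = 8.3%.
- q = 0.25: 0.0625/3 = 2.1%.

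With one list per site, one third holds again within each site. The values of q are assumptions, since the article does not give the split.

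**Step 4: alternatives.** Fixed sizes are exact. For mixed sizes, 60 patients were simulated 1,500 times, with an observer who knows the possible sizes and all past assignments but not the block boundaries.

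| Block sizes | Certain | Best guess right |
|---|---|---|
| 4 (as stated) | 33.3% | 70.8% |
| 6 fixed | 25.0% | 68.3% |
| 8 fixed | 20.0% | 66.6% |
| 2 and 4 | 11.0% | 72.1% |
| 2, 4 and 6 | 4.1% | 69.9% |
| 4 and 6 | 5.5% | 69.1% |
| 4, 6 and 8 | 2.1% | 67.8% |

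Varying the size removes most of the certainty. It lowers guessing accuracy only slightly, and mixes that include 2 do least on that measure.

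**Step 5: possible scale in kg, for illustration only.** Neither input is in the article. If the share of motivated patients differed by 10 to 30 percentage points between arms, and such patients lost 2 to 4 kg more, the bias would be 0.10 × 2 = 0.2 kg to 0.30 × 4 = 1.2 kg. The planned difference is 3.38 + 2.01 = 5.39 kg, so this is 0.2/5.39 = 4% to 1.2/5.39 = 22% of it.

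**The case against.** The strongest reply is that the design already has sound concealment and that one third is a worst case. The table is made independently and hidden, each assignment is revealed only after consent and BMI verification, and the principal investigator and the staff who weigh participants or obtain labs are blinded. No section says that a recruiter follows the running sequence. With two institutions on a shared list, a recruiter might see only part of it. This stands, and it is why one third is given as an upper limit with a lower range beside it.

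A reader might also infer that staff control when a patient is randomized. The article does not support that. The participant triggers verification, by photo or onsite weighing, and no section lets staff hold back a verified patient. What remains is influence over whom to pursue and how promptly a weight is processed, which is an inference.

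Nor is it right that such selection could never be addressed in the analysis. The Surveys section has all participants report motivation, interest and confidence about weight loss at baseline, so an imbalance could be seen and partly adjusted for. Selection on what the survey does not capture would remain.

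Finally, varied blocks hardly change best-guess accuracy. That is correct. The gain lies in removing certainty, which is what would make deliberate timing dependable.

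**Conclusion.** The point holds as an avoidable risk and a cheap improvement. The stated rule makes up to one third of assignments (an expected 20 of 60) certain to someone who sees the whole list and knows where blocks start. The share is about 8% to 19% if the sites share a list, each recruiter sees only own-site assignments, and that site contributes half to three quarters of the patients. It also assumes that recruiting staff learn past assignments; the article leaves them off the blinded list but does not say what they see.

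A reader might go further and conclude that concealment has failed or that the primary comparison is biased. The document does not support either. It states nothing wrongly here and contains no evidence of selection. The consequence is that the weight comparison could be biased, by an amount that the article gives no means to estimate.

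**What to change.** Have the same independent researcher regenerate the unused part of the allocation table with randomly varied block sizes, for example 4 and 6, or 4, 6 and 8. Withhold the sizes from recruiting staff and from documents they see. On the figures above, certain assignments fall from 33% to about 6% or 2%, and best-guess accuracy from 71% to about 69% or 68%.

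Two additions are better avoided. A block size of 2 has its second place always forced, and mixes that include it leave guessing accuracy at about 70% to 72%. Separate lists per institution could raise predictability, because a site recruiter would then see every earlier assignment in the list.

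The cost is a minor protocol amendment and a new upload to REDCap. The last block may be incomplete, so the final imbalance could reach half the largest block: 6/2 = 3 participants with sizes 4 and 6, or 8/2 = 4 with sizes 4, 6 and 8.
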